### Hypotheses

It is hypothesized that the condition that receives the mimicry task will show significantly better emotion recognition improvement scores (posttest minus baseline); the degree of alexithymia will negatively predict baseline scores; the degree of alexithymia will predict improvement scores (posttest minus baseline); when matched on alexithymia, the general population and ASD population will not significantly differ in emotion recognition improvement scores (posttest minus baseline); and when matched on alexithymia, the AM group and ASD group will not significantly differ on baseline emotion recognition scores.

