### Primary Outcome

The primary outcome being assessed is an increase in FEER. This will be measured by comparing the percent of correctly identified facial emotion expressions from the baseline assessment task to the instructed mimicry experimental task. Additionally, the percent of correctly identified expressions will also be compared between the control condition and the intervention condition. This will provide 2 primary metrics: before-after percent improvement and control group to experimental group percent improvement.

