### Intervention

The task will be delivered in-person at the Federation University Psychology Clinic in Ballarat, Australia, by the primary author in a small counselling room. The room will have 2 computers on a desk, each with separate monitors and peripherals (one for the participant and the other for recording eye-tracking data). Participants will take part in the task 1 participant at a time based on a mutually agreed upon time and date. Participants will only undergo this task once, and it is expected to take approximately 30 minutes based on prior testing where a small neurotypical group took approximately 25 minutes to complete the task in a usability test. The intervention is a software-based FEER training task that presents a series of different facial expressions and requires individuals to firstly mimic and then select which emotional expression they saw. The software runs on Microsoft Windows 10 and requires only minimal system requirements and a mouse.

The intervention task condition will begin with the software presenting a basic description of 6 facial expressions (fear, sadness, happiness, anger, disgust, surprise) and tips on how to spot each expression. Next, participants will be verbally advised by the experimenter and by on-screen text that a series of emotion recognition trials will begin shortly. Further, they will be told that after each emotion is displayed that they should try their best to mimic (copy) the observed facial expression with their own face. Once they have mimicked the expression, they should then use the 6 labelled buttons on the right-hand side (or associated keyboard shortcut) to choose which emotion was displayed. After selecting the answer using 1 of the 6 buttons, a 5-point Likert scale on the computer screen will ask the participant “How well did you mimic the expression?” with responses ranging from 1 “not very well” to 5 “very well.” This will repeat for each of the 36 trials. The trials will include various models of both men and women depicting the 6 emotions.

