The sequence of each trial in the task is depicted in Figure 2 with accompanying numbered indexes. Each trial will begin with a neutral expression image displayed on the screen (index 1). After this image has been displayed for 3 seconds, it will quickly swap to another image from the same model, except this image will depict an emotional expression (eg, angry or sad, index 2). After 500 milliseconds, this image will be replaced with the original neutral image (index 3), and the 6 buttons with emotion labels will appear on the right-hand side (index 4). Once the participant selects the emotion using the 6 buttons, the trial will conclude with the 5-point rating of how well the participant felt they copied the expression (index 5).

In a task that aims to test or train FEER ability, it is important to ensure that the emotional stimuli tested against are true exemplars of the emotion they purport to signal. It is also important that the expressive images in the baseline test and the experimental tasks are similar in recognition difficulty. This will reduce the risk of improvements being attributed to easier expressions in the experimental tasks compared to the baseline task. This task used the Warsaw Set of Emotional Facial Expression Pictures (WSEFEP) [57]. See Multimedia Appendix 3 for a description of these pictures and how pictures were selected for each condition. See Figure 2 for an example of the pictures.

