### Statistical Analyses

The data will be analyzed using SPSS, Version 25. Alexithymia will be analyzed to aid in matching the AM group and ASD group on alexithymia. To ensure that the ASD and AM groups, and also the experimental and control groups, are comparable, means and standard deviations of participant characteristics will also be compared with tests of difference.

The study design is a mixed factor, 2x2x2, within-between design (see Table 2), and therefore, the most appropriate test of difference is a mixed factorial ANOVA, set up according to Table 2 with IQ, depression, and anxiety variables added as covariates. This will provide analyses of whether the instructed mimicry intervention task was effective by comparing baseline scores to posttest scores. Additionally, it will provide the ability to compare posttest scores between the control group and the intervention group. Finally, this analysis will have the additional ability to discern these differences based on group (ASD group and AM group).

In addition to the mixed factorial ANOVA, a hierarchical regression analysis will also be conducted (see Table 3) to determine the predictive ability of alexithymia on the primary outcome variable.

**Table 2 table2:** Experimental group and intervention design.

Time point	ASD^a^ group (n=~32)		AM^b^ group (n=~32)	
	Control task condition (n=~16)	Mimicry task condition (n=~16)	Control task condition (n=~16)	Mimicry task condition (n=~16)
Pretest	FEER^c^ task score	FEER task score	FEER task score	FEER task score
Posttest (the intervention task is the posttest)	FEER task score	FEER task score	FEER task score	FEER task score

^a^ASD: autism spectrum disorder.

^b^AM: alexithymia-matched general population.

^c^FEER: facial emotion expression recognition.

**Table 3 table3:** Hierarchal regression stages for analysis.

Stage	Variables
Stage 1	IQ, age, gender
Stage 2	+Autism
Stage 3	+Alexithymia
Stage 4	+Intervention

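### If scores rise on average, alexithymia's lower baseline can by itself make it predict raw percent improvement, and the pooled main effect in Table 3 cannot tell this from extra benefit

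*Protocol article*

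**What the plan says.** All references are to the protocol article.

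- **Outcome.** Primary Outcome defines it by "comparing the percent of correctly identified facial emotion expressions from the baseline assessment task to the instructed mimicry experimental task". Under Intervention, the denominator is 36 six-choice items ("This will repeat for each of the 36 trials"). One item is therefore 1/36 = 2.8 percentage points, and guessing gives 1/6 = 16.7%.
- **Hypotheses.** Improvement is the raw difference, posttest minus baseline. Two predictions concern alexithymia: "the degree of alexithymia will negatively predict baseline scores" and "the degree of alexithymia will predict improvement scores (posttest minus baseline".
- **Models.** Under Statistical Analyses, the mixed ANOVA is run "with IQ, depression, and anxiety variables added as covariates"; alexithymia is not a term in it. A hierarchical regression is added "to determine the predictive ability of alexithymia on the primary outcome variable". Its stages (Table 3, "Hierarchal regression stages for analysis") are IQ, age and gender; then autism; then alexithymia; then intervention. There is no product term.
- **Purpose.** The Assessments section makes it part of the main aim to learn whether people with high alexithymia benefit more than others.
- **Safeguard.** Intervention says that baseline and experimental pictures should be equally hard. That guards against an easier posttest, not against gains that depend on the starting score.

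**The concern.** The two alexithymia hypotheses are linked through the baseline score. Someone who starts lower has more room to rise on a scale that stops at 100%. If everyone improves, through practice, the tips or the task, and gains shrink towards the top, the lower starters show larger percentage-point gains even when nobody benefits more in ability.

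Table 3 cannot separate these explanations. Alexithymia enters before intervention, so its coefficient is pooled over both arms and absorbs any general gain. A general gain is plausible in both arms, because controls also do the baseline task and then a second, closely similar one. At stake is the reading of a positive coefficient as evidence that the training suits people with alexithymia.

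**Working it through.** **1. The plan's own figure.** Sample Size Calculation gives 58 for f² = 0.27, 5% significance and 80% power. The overall F test of a regression with the six predictors of Table 3, with noncentrality 0.27 × N, gives N = 58 (power 0.808). Then 58 × 1.1 = 63.8, so 64. The figure reproduces and is unaffected by this point.

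**2. The mechanism.** Give two people the same log-odds gain of 0.5 (odds × e^0.5 = 1.649).
- From 75%: odds 3 × 1.649 = 4.95, or 83.2%, a gain of 8.2 points.
- From 90%: odds 9 × 1.649 = 14.84, or 93.7%, a gain of 3.7 points.

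The lower starter appears to gain about twice as much.

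**3. Simulation with equal log-odds gains.** The article gives no baseline mean, spread, alexithymia slope or retest gain, so these are assumptions: n = 58; 36 items per task; mean accuracy m of 70%, 80% or 90%; alexithymia lowering the log-odds of a correct answer by s = 0.3 or 0.5 per SD; residual person SD 0.4. For person i, baseline log-odds = logit(m) − s·aᵢ + eᵢ, and posttest log-odds = baseline + g, whatever the alexithymia score. Change was regressed on alexithymia and condition, with a two-sided 5% test and 2,000 runs per setting (Monte Carlo SE at 5%: √(0.05 × 0.95/2000) = 0.5 points).

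| Gain g | Raw percent change rejects | Empirical-logit change rejects |
|---|---|---|
| 0 | 4–6% | 5–7% |
| 0.3 in both arms | 8–19% | 5–7% |
| 0.5 in both arms | 14–40% | 4–7% |
| 0.5 control, 1.0 mimicry | 28–65% | 5–7% |

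At m = 80%, s = 0.5 and g = 0.5 (a mean gain of 7 points) the raw test rejects in 38%. Separate runs at baselines of 75–90% gave 8–20% for a gain of 0.3 and 27–66% for 0.7.

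**4. Equal percentage-point gains, cut off at 100%** (alexithymia slope 5–8 points per SD, person SD 6 points). Share of runs with a significant positive link, nominal 2.5%:
- baseline 70%, gain 5–10 points: 2–3%;
- baseline 80%, gain 10 points: 6–16%;
- baseline 90%, gain 10 points: 63–87%.

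**5. The reverse error.** A rise from 70% to 80% is ln(4) − ln(7/3) = 0.539 log-odds; from 80% to 90% it is ln(9) − ln(4) = 0.811. If true gains are equal in points, the log-odds scale makes lower starters look as if they gain less. With an equal 10-point gain at baselines of 70–80%, raw change rejected in 4–16% of runs and log-odds change in 26–51%, almost all in the negative direction.

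**6. An alexithymia-by-condition term** on raw change rejected in 4–7% of runs when both arms gained equally. With gains of 0.5 and 1.0 log-odds in the two arms it rejected in 7–12%, and other unequal-gain runs gave 10–19%. On the log-odds scale, with additive gains that differed by arm, it rejected in 20%.

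**7. Adding baseline as a linear covariate** does not repair the test. With no gain at all, the adjusted alexithymia slope was −1.8 to −4.9 points per SD and was significant in 49–88% of runs, because baseline is measured with error.

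**The case against.** The strongest reply is that the inflation in step 3 follows from defining an equal gain on the log-odds scale. Percent correct is the stated outcome, a gain in percent correct is a legitimate target, and nothing in the article says on which scale gains are equal. This stands. Step 5 shows that replacing percent change with log-odds change can create a spurious effect of its own, so neither scale is safe alone.

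A second reply is that scores near ceiling are not established. This also stands. That the pictures "are true exemplars of the emotion they purport to signal" concerns whether they signal the right emotion, not how easy they are. Each expression is shown for only 500 ms, and picture selection is described in Multimedia Appendix 3, which is not at hand.

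A third is that models for proportions are often left to an analysis plan. This stands only for the choice of transformation. The article itself fixes the difference score, the hypothesis and the regression stages, and those stages cannot answer the extra-benefit question on any scale.

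Three stronger readings might be inferred and are not supported:
- *A lower baseline alone creates the link.* It does not: with no average gain the test keeps its nominal level.
- *The main efficacy result is biased.* It is not: randomisation balances headroom between the arms in expectation.
- *The ASD-versus-AM comparison of improvement is distorted in the same way.* The groups are matched on the number meeting the alexithymia cut-off, and the plan predicts no baseline difference between them, so on its own premises there is little headroom difference to act on.

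**Conclusion.** The point holds in conditional form. If scores rise on average and gains shrink near the top of the scale, the hypothesised lower baseline can by itself make alexithymia predict raw improvement. The pooled main effect in Table 3 could not tell this from extra benefit.

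Under equal log-odds gains of 0.3 to 0.5 in both arms, the nominal 5% test rejects in 8–40% of trials. With no gain, or with additive gains well below ceiling, there is no such artefact. These sizes rest on assumed baselines, slopes, spread and gains; the article supplies none of them, so the true size is unknown. The point affects the alexithymia-improvement hypothesis and the extra-benefit aim.

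**What to change.** 1. Base the extra-benefit question on an alexithymia-by-condition term for improvement (by time, in a repeated-measures model), not on the pooled main effect. This removes most of the inflation when both arms gain alike, but it still depends on scale when their gains differ.
2. Keep percent correct as the stated outcome. Beside it, analyse the item-level correct/incorrect answers with a logistic mixed model that has random intercepts for participant and picture, and show model-based percentages with the odds ratios.
3. Claim that alexithymia modifies improvement only if the result has the same direction and holds on both the percent and the log-odds scale.
4. Do not rely on a linear baseline covariate as the remedy.

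**Cost.** One extra model, a change of analysis wording and a stricter condition for the alexithymia-improvement claim; no new data. The timeline states that recruitment had not begun as of June 2021. The sample size was not set for the interaction: a seventh predictor moves the overall-model calculation from 58 to 61, and no effect size is assumed for the term itself, so its power is unknown and its estimate should be reported with a confidence interval.

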### Study Aims

The first aim of this study is to evaluate the efficacy of an instructed mimicry task condition to improve FEER compared to a control condition and also from baseline to posttest in adults with and without alexithymia and ASD. The second aim of the study is to confirm findings by Cook et al [32] that FEER is related to alexithymia and not ASD. As an ancillary aim, the study will also collect data for further research on how eye-gaze patterns in type 1 alexithymia and type 2 alexithymia uniquely relate to FEER in the same sample.

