### Participants

We will recruit through local ASD support groups, online social media, and noticeboard advertisements (eg, at Federation University Australia). We will also use snowball recruiting to better penetrate the ASD community. Participants with an ASD (based on the assessments described in the Assessment section) will be assigned to the ASD group. Other participants will be assigned to the alexithymia-matched general population group (AM group).

The researchers will also use the 20-item Toronto Alexithymia Scale (TAS-20) total scores [40] to match the ASD group with the AM group without an ASD. Specifically, the number of participants in each group meeting criteria for alexithymia will be matched as indicated by TAS-20 scores ≥61, which is how groups have been matched in similar studies (eg, [32]).

The inclusion criterion is that participants are 18 years of age and older. The ASD group also has the added inclusion criterion of a confirmed ASD based on the assessment described in the Assessment section. Exclusion criteria include the participant having another mental health condition (other than an ASD if in the ASD group) diagnosed by a clinician and that the Kessler Psychological Distress Scale (K10) [41] indicates a significant level of distress (cut-off score of 22).

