### Sample Size Calculation

Based on the effect sizes of 2 previous studies measuring similar constructs and similar tasks [32,35], to achieve a medium to large effect (eg, Gpower f^2^ test = 0.27) with a significance of 5% (*P*=.05) and power of 80%, a sample size of 58 will be required to demonstrate statistical significance for the primary hierarchal regression and analysis of variance (ANOVA). Given an expected attrition of 10%, a total of 64 participants will be recruited.

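### Two hypotheses and the 'not ASD' half of Aim 2 count a non-significant ASD v AM difference as support, although about 32 v 32 people cannot rule out a medium-sized difference

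*Protocol article*

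**What the plan says.** The Hypotheses section of the protocol article lists five hypotheses. The fourth is that, after matching on alexithymia, "the general population and ASD population will not significantly differ in emotion recognition improvement scores". The fifth is that "when matched on alexithymia, the AM group and ASD group will not significantly differ on baseline emotion recognition scores". The second aim in Study Aims is to confirm a published study's result "that FEER is related to alexithymia and not ASD".

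Statistical Analyses names two methods. One is a mixed factorial ANOVA, presented as a test of difference, with IQ, depression and anxiety as covariates. The other is a hierarchical regression (Table 3) that enters autism at stage 2 and alexithymia at stage 3, aimed at the primary outcome variable. Primary Outcome defines that variable as an increase in FEER. Neither method comes with a margin or a confidence-interval rule.

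Sample Size Calculation states that "a sample size of 58 will be required to demonstrate statistical significance for the primary hierarchal regression and analysis of variance (ANOVA"), and recruits 64 to allow for 10% attrition. Table 2 gives about 32 ASD and about 32 AM participants.

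On matching, Participants says that "the number of participants in each group meeting criteria for alexithymia will be matched", using a TAS-20 score of 61 or more. For comparability of the groups, "means and standard deviations of participant characteristics will also be compared with tests of difference".

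**The concern.** A hypothesis that two groups will not differ significantly is met whenever the test fails to reject. A failure to reject can mean that the groups are alike, or that the study was too small or too noisy to tell them apart. Under this wording, the smaller the trial and the less precise the FEER score, the more often the two hypotheses are met. The criterion is written into the hypotheses themselves, so it is not a detail that a condensed article leaves to a SAP.

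At stake is the statement that FEER difficulty does not belong to ASD once alexithymia is accounted for. A real ASD deficit of moderate size could be reported as absent.

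A second weakness sits in the same contrast. Matching equalises only how many people in each group pass a cut-off on a scale that runs from 20 to 100. Mean TAS-20 scores can still differ between groups with equal counts, and the ANOVA does not carry the score.

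**Working it through.** **The plan's own figure.** Inputs from Sample Size Calculation: f² = 0.27, alpha 5%, power 80%. Table 3 lists six predictors (IQ, age, gender, autism, alexithymia, intervention). For the overall regression test, the noncentrality is f² × N = 0.27 × 58 = 15.66 with 6 and 51 degrees of freedom. Power is 0.808, and 58 is the smallest N that reaches 80%. So 58 reproduces as a test that the six predictors jointly explain something. It says nothing about showing that the ASD and AM groups are alike.

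**Inputs for the ASD v AM contrast.** n = 32 per group (Table 2), or 58/2 = 29 per group after the planned attrition. The test is two-sided at 5% (sidedness is not stated and is assumed). No adjustment for covariates is made, because the document gives no correlations. True differences d, in SD units of the score concerned, are assumed; the document gives none for this contrast.

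**Precision.** The standard error in SD units is √(2/n): 0.250 for n = 32 and 0.263 for n = 29. The 95% half-width is t(0.975, 2n−2) × √(2/n):
- n = 32: 1.999 × 0.250 = 0.50 SD
- n = 29: 2.003 × 0.263 = 0.53 SD

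**Chance of a non-significant result when a difference exists.** Noncentral t with noncentrality d/√(2/n). At d = 0.5 and n = 32 this is 0.5/0.250 = 2.00, almost equal to the critical value 1.999, hence power close to one half.

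| True d (assumed) | Missed, 32 v 32 | Missed, 29 v 29 |
|---|---|---|
| 0.2 | 88% | 88% |
| 0.3 | 78% | 80% |
| 0.5 | 50% | 54% |
| 0.8 | 12% | 15% |
| 1.0 | 2% | 4% |

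The difference detectable with 80% power is 0.71 SD (32 v 32) or 0.75 SD (29 v 29).

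**What the sample could show by equivalence.** Two one-sided tests at 5% each, true difference zero. The margin giving 80% power is approximately [t(0.95) + t(0.90)] × √(2/n):
- n = 32: (1.670 + 1.295) × 0.250 = 0.74 SD
- n = 29: (1.673 + 1.297) × 0.263 = 0.78 SD

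With a margin of 0.5 SD, simulated power is 26% (32 v 32) or 19% (29 v 29). About 69 per group would be needed for 80% (normal approximation).

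**The case against.** Several points on the other side stand.

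- **The ANOVA is not the only tool.** A reader might infer that alexithymia is never adjusted for. Table 3 enters both autism and alexithymia, so from stage 3 the autism coefficient is adjusted for alexithymia. That partly answers the matching problem for improvement scores. As written, the regression targets only the primary outcome. The hypothesis that alexithymia predicts baseline scores suggests a baseline model too, but none is stated. The regression has no rule for concluding absence of a difference either.
- **Aim 2 is not wholly a null prediction.** Its alexithymia half is a positive hypothesis, and low power works against it. Only the 'not ASD' half gains from imprecision.
- **This is not the trial's main claim.** Assessments gives the main aim as efficacy of the intervention. ASD v AM is a non-randomised contrast.
- **The miss rates depend on assumed differences.** The sample size assumes a medium to large effect. If f² = 0.27 applied to this single contrast, d would be 2 × √0.27, about 1.0, and would be missed only 2-4% of the time. The planned covariates could also raise power, by an amount that cannot be computed here.
- **The size of any residual confounding is unknown.** The document gives neither the TAS-20 imbalance that would remain nor the TAS-20 to FEER correlation. Comparing group means, as planned, might reveal an imbalance, but it does not adjust for one.

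The Discussion concedes that separating ASD from alexithymia will be hard. Its reason is that matching may bring in other confounders, which is a different issue from reading non-significance as equality.

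**Conclusion.** The concern holds for the fourth and fifth hypotheses and for the 'not ASD' half of Aim 2. At the planned size, non-significance leaves room for differences of medium size or larger: the 95% half-width is 0.50-0.53 SD, and a true 0.5 SD difference would be missed about half the time. These figures assume an unadjusted two-sided 5% comparison and the stated values of d.

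The documents do not support going further. They do not show that the whole of Aim 2 would be confirmed by low power, that the efficacy result is compromised, or that count-matching leaves a bias of any particular size. The randomised mimicry v control comparison is unaffected.

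**What to change.** 1. Reword the fourth and fifth hypotheses so that a non-significant test is not confirmation. Report the ASD minus AM difference in baseline and improvement scores with its confidence interval.
2. Claim no meaningful difference only if the 90% interval lies inside a margin justified and fixed before recruitment; otherwise report the result as inconclusive. If no margin can be justified, report the difference and its interval and drop the word confirm. This alone would cure the defect.
3. State that about 64 people give 80% power only for margins of roughly 0.75 SD or more. The document gives no SD for FEER, so this cannot yet be turned into percentage points.
4. Add the continuous TAS-20 total to the ASD v AM contrasts, explicitly including the baseline contrast.

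The cost is wording, one decision rule and one covariate already collected at screening. The article says recruitment had not begun as of June 2021. The downside is a less favourable claim: with a margin near 0.5 SD the answer would usually be inconclusive, and a non-significant result could no longer be presented as support.

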### Randomization

Participants will be randomized using permuted block randomization with stratification across age and gender to receive either the control or experimental task condition with equal numbers from both the ASD group and AM group receiving each task.

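### The ASD v AM comparison of baseline FEER is not adjusted for age or gender, because the plan's age- and gender-adjusted regression is tied to improvement rather than to baseline

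*Protocol article*

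**What the plan says.** All references are to the protocol article.

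- **Hypotheses.** The fifth hypothesis is that "when matched on alexithymia, the AM group and ASD group will not significantly differ on baseline emotion recognition scores". The second is that a higher degree of alexithymia goes with lower baseline scores. Together they serve the second of the Study Aims, to show that FEER is related to alexithymia rather than to ASD. The fourth hypothesis makes the no-difference claim for improvement scores.
- **Participants.** The AM group is made comparable to the ASD group on one feature: "the number of participants in each group meeting criteria for alexithymia will be matched as indicated by TAS-20 scores ≥61".
- **Randomization.** The method is "permuted block randomization with stratification across age and gender to receive either the control or experimental task condition".
- **Statistical Analyses, ANOVA.** The test of difference is a "mixed factorial ANOVA, set up according to Table 2 with IQ, depression, and anxiety variables added as covariates". Table 2 includes the pretest score and the ASD and AM groups.
- **Statistical Analyses, Table 3.** A hierarchical regression is planned "to determine the predictive ability of alexithymia on the primary outcome variable". It enters IQ, age and gender at Stage 1, then Autism, Alexithymia and Intervention. The Primary Outcome section defines the primary outcome as an increase in FEER.
- **Other safeguards.** Participant characteristics are to be compared between the ASD and AM groups by tests of difference. The Discussion concedes that matching on alexithymia may bring in other confounders.

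**The concern.** People recruited through ASD support groups and general-population volunteers may differ in age and gender mix. If either variable is related to FEER, the crude group difference at baseline mixes that relation with any effect of ASD. Such a bias can produce an apparent ASD deficit, or hide a real one. The second case matters more here, because the fifth hypothesis predicts no difference and a masked deficit would look like confirmation. A larger sample does not shrink a bias of this kind.

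The sponsor treats both variables as things to control for: they stand at Stage 1 of Table 3, and Table 1 lists demographics among the control variables. Their absence from the covariate list of the only analysis stated to contain the baseline group contrast is an inconsistency within the plan. It is not a detail left for later, since the article does state that list.

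**Working it through.** **1. What controls age and gender, and for which comparison**

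| Comparison | Randomised? | Age and gender in the design | Age and gender in the stated analysis |
|---|---|---|---|
| Mimicry v control task | Yes | Stratified | Table 3 yes, ANOVA no |
| ASD v AM, improvement (4th hypothesis) | No | No | Table 3 yes (Autism enters after Stage 1), ANOVA no |
| ASD v AM, baseline FEER (5th hypothesis) | No | No | ANOVA no; Table 3 not stated for this outcome |

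Only the last row lacks control in both design and analysis.

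**2. The plan's own sample size**

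Inputs from Sample Size Calculation: f² = 0.27, alpha 0.05, power 80%, N = 58. For an omnibus regression test with k predictors, the noncentrality is f² × N, on k and N − k − 1 degrees of freedom. The required N is 54 for k = 5, 58 for k = 6 (power 80.8%) and 61 for k = 7. Table 3 holds six variables: IQ, age, gender, autism, alexithymia and intervention. The article does not state the number of predictors, but 58 is what a model including age and gender requires.

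**3. Possible size of the bias (assumed inputs; the article gives none)**

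- Gender: difference in proportion male × gender effect in SD. From 0.1 × 0.1 = 0.01 SD to 0.5 × 0.5 = 0.25 SD.
- Age: age difference in SD × correlation of age with FEER. From 0.25 × 0.1 = 0.025 SD to 1.0 × 0.3 = 0.30 SD.

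The two may add or partly cancel.

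**4. Effect on the test of the fifth hypothesis**

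With 32 v 32, the standard error of a standardised difference is √(2/32) = 0.25. A bias of b SD gives noncentrality b/0.25 = 4b. Using a two-sided 5% t test with three covariates (64 − 2 − 3 = 59 degrees of freedom) and no true ASD effect:

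| Bias (SD) | Rejection rate |
|---|---|
| 0 | 5.0% |
| 0.05 | 5.4% |
| 0.10 | 6.8% |
| 0.15 | 9.1% |
| 0.20 | 12.3% |
| 0.30 | 21.9% |

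For masking, a bias of 0.3 SD against a true deficit of 0.5 SD leaves an apparent difference of 0.5 − 0.3 = 0.2 SD. The chance of detection falls from 50.3% to 12.3%.

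**5. Would the tests of difference catch an imbalance?**

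At 32 v 32, a two-sided 5% test on gender has about 37% power for 50% v 70% and about 54% for 50% v 75%. A real imbalance would often be missed, and the article attaches no action to a positive result.

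**6. Cost of adjusting**

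Going from three to five covariates lowers the residual degrees of freedom at N = 64 from 59 to 57. Counting only that cost:

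| N | d | Power, 3 covariates | Power, 5 covariates |
|---|---|---|---|
| 64 | 0.5 | 50.3% | 50.3% |
| 64 | 0.8 | 88.3% (0.8825) | 88.2% (0.8821) |
| 58 | 0.5 | 46.4% | 46.3% |
| 58 | 0.8 | 84.9% | 84.8% |

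**The case against.** **Table 3 may be meant for baseline too.** The second hypothesis needs a regression on baseline scores, and Table 3 is the only regression described. Without Intervention, Stages 1 to 3 form a sensible baseline model in which Autism is adjusted for age and gender. The article is also loose about its primary outcome: Table 1 gives the measure as FEER ability, marked at pretest and during the task, and the Discussion calls the primary variable simply emotion recognition. This has weight, and the sponsor may intend it. But Primary Outcome defines an increase, Table 1 names an improvement score as the instrument, and Stage 4 cannot apply to a score taken before randomisation. Nowhere does the article say that Stages 1 to 3 are fitted to baseline FEER.

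**The risk is checked and admitted.** The tests of difference and the Discussion's caveat show that the sponsor sees the problem, and the caveat tempers how a null result would be read. Neither removes the bias, and no remedy is given for two confounders that are already measured.

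**The size is assumed.** This stands in full. At the low end of the range the effect on the test is negligible, and opposing age and gender effects could cancel.

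**Conclusion.** The point holds for baseline FEER. The two analyses carry different covariate sets, and the one containing age and gender is tied to improvement. As written, the non-randomised baseline contrast of the fifth hypothesis is unadjusted for both.

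A reader might infer more than the article supports:

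- *That age and gender are ignored for ASD v AM throughout.* They are not. On improvement, Table 3 gives an Autism term adjusted for both, so for the fourth hypothesis only the ANOVA version is unadjusted.
- *That the second aim stands or falls with the fifth hypothesis.* The second hypothesis carries the other part.
- *That a bias of a particular size is present.* Neither size nor direction can be derived from the article. The range of about 7% to 22% for the rejection rate rests on assumed biases of 0.1 to 0.3 SD, no true ASD effect and 32 per group.
- *That the mimicry v control contrast is biased.* Task is randomised with stratification by age and gender, so it is outside this point.

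**What to change.** Choose one of the following and state it before data are seen. The Timeline section reports that recruitment had not begun as of June 2021.

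- Add age and gender to IQ, depression and anxiety as covariates in the ANOVA for the ASD v AM comparison; or
- State that Stages 1 to 3 of Table 3 are also fitted to baseline FEER. The same run would also serve the second hypothesis.

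In either case, adjust whatever the tests of difference show, and report the adjusted ASD-minus-AM baseline difference with its 95% confidence interval, with the unadjusted difference beside it.

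The cost is a sentence in Statistical Analyses and about two residual degrees of freedom. Demographics are already collected at online screening, and no change of sample size is needed. Two limits remain. The power figures count degrees of freedom only, so a strong association of age or gender with group would widen the interval somewhat. Adjustment also does nothing about unmeasured confounders, so the Discussion's caveat should stay.
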